#### Sample size calculation

We based our sample size calculation on the primary outcome, the Kujala score. To date, no high-quality study (randomized trial) on the difference in change in Kujala score between dynamic and static MPFL reconstruction is available. However, in a prospective randomized control trial, Kang et al. [56] compared two different tensioning techniques for static MPFL reconstruction. They reported an effect size of 7.8 for the improvement in the Kujala score for both groups and a group difference in change in Kujala score of 1.9. Based on biomechanical considerations, we expect a larger improvement in patients stabilized using the dynamic MPFL reconstruction. Assuming a 3.8-point improvement in the Kujala score in patients with dynamic MPFL reconstruction compared to patients with static MPFL reconstruction, 54 patients (27 per group) are required to detect a significant difference in change in Kujala score between the two groups with 80% power at a significance level of 5%. We expect a dropout rate of about 10%, and will thus we will target a study cohort of 60 patients (30 per group).

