**Fig. 1 Fig1:**
[figure not shown]
Native anatomy, static and dynamic MPFL reconstruction

Several studies have addressed the challenges of correct isometric graft tensioning by evaluating the appropriate load and manner of optimal graft tension during surgery and ways of determining the optimal length and elasticity of the graft [24, 26]. As an alternative to static reconstructions, more elastic insertion techniques with soft tissue fixation only have been suggested [29–33] where the static graft is attached to soft tissue allowing small movements. The medial patellotibial ligament (MPTL) is considered as another restraint of patellar stability and often reconstructed as well in soft tissue fixation procedures [33, 34]. Becher et al. [29] have suggested that not only a dynamic insertion but also a dynamic rather than a static graft should be used for stabilizing the patella. They described a fully dynamic MPFL procedure by detaching and reinserting only the distal part of the gracilis muscle to the patella and leaving the proximal tendon attached to its muscle presumably facilitating dynamic adjustment of the patellar position by muscle contraction (Fig. 1). In a retrospective cohort study, Becher et al. [29] reported comparable mean outcomes of static and dynamic MPFL reconstruction are measured by Kujala, Tegner and Lysholm scores with large variability among groups. The advantage of this dynamic graft procedure is an improved physiological reconstruction of the MPFL as a mostly dynamic structure. Moreover, several surgical steps of the static MPFL reconstruction are avoided, and the dynamic MPFL procedure is therefore faster, simpler and more cost effective. While the advantages of shorter and more forgiving surgical technique in the Becher's procedure seem to make it preferable to other techniques, to date high-quality data on clinical and functional outcomes are lacking.

In this prospective, single blinded, randomized, multicenter clinical trial, we will compare clinical and biomechanical outcomes of static MPFL reconstruction according to Schöttle et al. [20] and dynamic MPFL reconstruction according to Becher et al. [29] up to 2 years after surgery.

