#### Statistical analysis

The study involves a series of quantitative outcomes and different types of hypotheses. Hypotheses about differences between patients treated with dynamic or static technique will be addressed by describing and visualizing the distribution of the corresponding variables in each patient group and by quantifying the group differences by the difference in mean values with 95% confidence intervals and p-values. Hypotheses concerning the association between two variables will be addressed by visualizing the joint distribution of variables in scatter plots and quantifying the association by partial correlations coefficients with 95% confidence intervals. Hypotheses concerning a change over time will be addressed by visualizing the distribution of individual differences and quantifying the change over time by the mean difference with 95% confidence intervals and p-values. Hypotheses concerning the association in change over time between two variables will be addressed by visualizing the joint distribution of differences in scatter plots and quantifying the association by correlations coefficients with 95% confidence intervals. In addition, the relation to baseline values will be examined. Patient characteristics will be tabulated for each patient group.

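### The 80% power with 27 per group rests on an unstated SD of Kujala change of about 4.9 points, so the power is not established; baseline adjustment would gain precision at no cost

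*Protocol article*

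**What the plan says.** All the planning figures are in the protocol article, section "Sample size calculation". The outcome is fixed first: "We based our sample size calculation on the primary outcome, the Kujala score". The target follows: "Assuming a 3.8-point improvement in the Kujala score in patients with dynamic MPFL reconstruction compared to patients with static MPFL reconstruction". The result is that "54 patients (27 per group) are required to detect a significant difference in change in Kujala score between the two groups with 80% power". The test is at the 5% level, and the number is raised to 60 patients for about 10% dropout.

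The source is a randomised trial of two tensioning techniques for static reconstruction. Two of its figures are given. One is a between-group difference in change of 1.9 points. The other is described thus: "They reported an effect size of 7.8 for the improvement in the Kujala score for both groups". The 7.8 has no unit and no definition. No SD of change, and no standardised between-group effect, appears anywhere in the article.

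For the analysis, the section "Statistical analysis" plans "quantifying the group differences by the difference in mean values with 95% confidence intervals and p-values". It adds that the relation to baseline values will be looked at, but does not make baseline part of the group comparison. Table 1 shows the Kujala score collected before surgery and at all five follow-ups.

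**The concern.** A two-group comparison of means needs four inputs to give a sample size: difference, SD, power and significance level. Here three are stated and the SD is missing, although the result depends on it strongly: the required number per group grows with the square of the SD. A reader cannot tell whether 27 per group came from a sound SD of change, from a standard error, or from the 7.8 used in some way.

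The stake is how the primary result will be read. If the true SD is near 4.9 points, the trial has the power it claims for 3.8 points. If it is larger, a non-significant result says much less about a 3.8-point difference than the stated 80% suggests.

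**Working it through.** **Inputs.** From "Sample size calculation": difference 3.8 points, 27 per group, power 80%, significance level 5%, dropout about 10%. Sidedness is not stated; I take two-sided, in line with the 95% confidence intervals in "Statistical analysis", and show one-sided as well. The test is taken to be a two-sample t test on change.

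**Dropout step.** 54 / 0.9 = 60. This reproduces.

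**The plan's 27 per group.** It cannot be computed forwards without an SD, so I solved for the SD that gives it. With n per group, the test has 2n − 2 = 52 degrees of freedom and non-centrality (3.8 / SD) × √(n/2). Power of 80% at n = 27 needs a standardised difference of 0.777.

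- Two-sided t test: SD = 3.8 / 0.777 = 4.89.
- Two-sided normal approximation: SD = 3.8 / [(1.960 + 0.842) × √(2/27)] = 4.98.
- One-sided 5% t test: standardised difference 0.686, so SD = 3.8 / 0.686 = 5.54.

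**Can the 7.8 supply this SD?** There are three readings.

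1. *An SD in points.* The standardised difference is 3.8 / 7.8 = 0.487. Power at 27 per group is 42%, and 68 per group are needed for 80%.
2. *A standardised effect (mean change divided by its SD).* An SD of 4.89 then requires a mean gain of 7.8 × 4.89 = 38.1 points, which the article does not state. Other assumed gains give:

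| Assumed mean gain (points) | SD = gain / 7.8 | Power at 27 per group |
|---|---|---|
| 30 | 3.85 | 95% |
| 35 | 4.49 | 86% |
| 40 | 5.13 | 76% |
| 45 | 5.77 | 66% |

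3. *A mean change in points.* It then carries no information on the SD.

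**Power and detectable difference at 27 per group** (two-sided t test). The detectable difference at 80% power is 0.777 × SD. Apart from the back-solved 4.89, the SDs are assumptions, because the article gives none.

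| SD of change | Power for 3.8 points | Detectable difference |
|---|---|---|
| 4.89 (back-solved) | 80% | 3.8 |
| 6 | 63% | 4.7 |
| 7.8 | 42% | 6.1 |
| 10 | 28% | 7.8 |

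**Gain from baseline adjustment.** Assume equal variances before and after surgery and correlation r between the two scores. Relative to a comparison of change scores, analysis of covariance (ANCOVA) multiplies the standard error by √[(1 − r²) / (2(1 − r))] = √[(1 + r) / 2]. At r = 0.8 this is √0.90 = 0.949, about 5% smaller. At r = 0.3 it is √0.65 = 0.806, about 19% smaller. The correlations are assumptions.

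**The case against.** The strongest reply is that nothing in the article contradicts an SD of 4.9. The words used for the 7.8 point most naturally to a standardised effect, and on that reading the claimed 80% lies inside the range in the first table. The 42% and 68-per-group figures need the words to be read against their usual meaning, and only the cited trial, which is not at hand, could settle it. This stands, and it rules out the conclusion that the trial is underpowered.

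A reader might also infer that the SD must be well above 4.9 from the Background, where an earlier retrospective cohort "reported comparable mean outcomes of static and dynamic MPFL reconstruction are measured by Kujala, Tegner and Lysholm scores with large variability among groups". That does not follow. The remark has no number, covers three scores, and does not mention change, whose SD can differ from that of the scores themselves. Nor is doubling 1.9 to 3.8 an error: the article discloses it as an assumption and gives a reason.

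The last objection is that this is a journal article and the SD may stand in the full protocol. If the missing SD were the whole point, it would be a request for detail. Two things remain. The article sets out the calculation with its source and other inputs, and the one figure it offers in the SD's place is undefined. The analysis it describes is a plain difference in means that leaves baseline information unused.

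**Conclusion.** The claim of 80% power is not established. It holds if the SD of Kujala change is about 4.9 points (two-sided) or 5.5 (one-sided), and the article neither states nor justifies either value. The readings of the 7.8 that can be computed span 42% power (as an SD) to between 66% and 95% (as a standardised effect with assumed gains of 45 down to 30 points). A reader might conclude from the lower figures that 60 patients are too few. The documents do not support that, since every SD other than the back-solved one is an assumption. All figures assume a two-sample t test on change with 27 analysed per group.

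Adjusting for baseline is worthwhile whatever the SD turns out to be. On the assumptions shown it reduces the standard error by about 5% to 19% relative to change scores, with no new data.

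**What to change.** Keep 60 patients and make two changes.

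1. Analyse the primary Kujala comparison by ANCOVA, with the baseline Kujala score as covariate, in place of the unadjusted difference in mean change. Report the adjusted difference with its 95% confidence interval and p-value.
2. Rewrite the sample size paragraph. Define the 7.8, state the SD of change with its source, and confirm that it is an SD and not a standard error or a standardised effect. State the test and its sidedness. Replace the single 80% claim with power and detectable difference at 27 per group over a range of SDs labelled as assumptions, for example 63% and 4.7 points at SD 6, 42% and 6.1 points at 7.8, and 28% and 7.8 points at 10.

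A blinded look at the pooled SD during the trial, used only to restate the detectable difference, is optional.

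The cost is one paragraph on sample size and one sentence on analysis. No patients, visits or measurements are added. The stated power may look less favourable once the SD is given.

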## Discussion

The proposed study will provide the first biomechanical data on the muscle transfer procedure for dynamic MPFL reconstruction and compare these with the established static reconstruction technique. The results of this study can be considered as a first randomized trial evaluating the effectiveness of both techniques and providing evidence for surgery decision-making. Pre- and postoperative biomechanical evaluations will be performed to assess muscle strength and lower extremity kinematics, kinetics and timing and intensity of muscle activity during gait. Most biomechanical studies on the patellofemoral joint focus on describing the static patellar position and joint reaction force by using methods such as computer tomography [57], MRI [58] or cadaveric studies [59] without acknowledging dynamic muscle driven knee motion. This is important to consider in the muscle transfer procedure of dynamic MPFL reconstruction: we anticipate that the gracilis muscle activity will adapt to its new role as patella stabilizer. The capability and efficacy of muscle transfer procedures have been described for other procedures such as rectus femoris transfer in children with cerebral palsy [39, 40]. The gracilis muscle reaches forces up to 300 N from 0° to 60° knee flexion y^41^ indicating that the gracilis muscle is adequate for patella stabilization. With this study, we will provide much needed information on knee biomechanics after dynamic versus static MPFL reconstruction to provide evidence to support orthopedic surgeons in evidence-based decision-making in their quest for surgical techniques most favorable for their patients.

## Data Availability

Not applicable.

## Abbreviations

MFPL: Medial patellofemoral ligament
MRI: Magnetic resonance imaging
AGA: Society for Arthroscopy and Joint-Surgery
PIS: Patella instability severity score
